### Sample size

We calculated the required sample size based on data from a previous study [21]. Sample size calculation was performed with the G*Power V.3.1.9.2 software [22], using the *F* test between the factors with four groups (modified-Paleo diet with calorie counting, modified-Paleo diet with a fixed diet plan, medium-carbohydrate diet with calorie counting, and medium-carbohydrate diet with fixed diet plan) and two evaluation sessions (before and after intervention). According to the mean difference in the change in body weight (11 kg) and standard deviation of 15 (by assuming equal standard deviation in groups) [21], the calculated effect size *f* is 0.39. We considered an *α* error probability of 0.05 and a power (1-*β* error probability) of 0.80. We take the correlation among repeated measures as 0.6. The resulting total sample size is 60, meaning 15 in each intervention group. Allowing for a maximum dropout rate of 30%, the final number of subjects in each treatment group has been set to 20 participants. The study is registered on the Iranian Registry of Clinical Trials website (http://www.irct.ir, identifier: IRCT2016121925267N4). This study was reported based on the recommended checklists for clinical trials [23, 24] (Additional file 1).

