### Study outcomes

In the present study, we have multiple primary outcomes due to the nature of the dietary interventions as seen in many other randomized clinical trials [18, 19]. A single outcome may be insufficient to fully describe the effects of an intervention on a complex disease, namely metabolic syndrome. Weight, body composition, and CTRP6 (as an inflammatory marker) are the main primary outcomes in the current study. Sample size calculation has been estimated on the body weight changes as the largest number achieved in each group. Hence, our primary endpoints will be the mean difference in the changes from baseline to 10-week follow-up in body composition component (weight and body fat mass) and CTRP6 concentration between the intervention groups. Study success will be declared if either one of the primary endpoints will be statistically significant in favor of the experimental treatment.

The main secondary outcomes would be lipid profile, glycemic indices, serum insulin, leptin, and plasma EMPs (CD31+/CD42b− and CD144+/CD42b−). Satiety, hunger, fullness and desire to eat [20], inflammatory factors (chemerin, FGF-21, Asprosin), PYY, ghrelin, and creatinine are exploratory outcomes.

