### Statistical analysis

Statistical analyses of all data will be performed using STATA version 12.0 (Stata Corp LP, College Station, TX). The intention-to-treat approach will be used for data analysis in order to handle non-adherence. Data will be expressed as mean (SD). The one-sample Kolmogorov–Smirnov test will be used to verify the normality. If a variable distribution is not normal, the log transformation will be applied. An analysis of variance (ANOVA)/analysis of covariance (ANCOVA) model will be used to compare the values among the four intervention groups. Analysis of variance (ANOVA) and post hoc Bonferroni correction will be used for multiple comparison adjustment. Since we have 4 intervention groups (1, modified-Paleo diet with calorie counting; 2, modified-Paleo diet with a fixed diet plan; 3, medium-carbohydrate diet with calorie counting; and 4 medium-carbohydrate diet with a fixed diet plan), we will have six possible pairwise comparisons across the groups (1 with 2, 1 with 3, 1 with 4, 2 with 3, 2 with 4, 3 with 4). By these primary comparisons, we will be able to compare the effects of diets (low vs moderate carbohydrate) and delivery modes (calorie counting vs fixed diet plan) on primary outcomes. Further, there are two modules, by which confidence intervals can also be adjusted along with *p*-value for multiple comparisons. “Pwmean” and “pwcompare” modules allow for performing all pairwise comparisons using Tukey, Bonferroni, or Dunnett. An analysis of covariance (ANCOVA) will be applied to adjust the effects of confounding and baseline variables. *p* < 0.05 (two-sided) will be considered as statistically significant. Besides the null hypothesis significance testing (NHST), appropriate effect size and its 95% confidence interval will also be analyzed to provide more reasonable justification about results. Cohen’s *d* effect size, measured as the mean difference in change divided by the pooled standard deviation of the change, will be reported along with its 95% CI. Cohen’s *d* is defined as standardized mean difference (SMD) and is classified as small (*d* = 0.2), medium (*d* = 0.5), or large (*d* = 0.8) [27]. Multiple imputation will be used to correct missing data. The SAMPL guideline will be used for statistical analysis in this study [28].

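### The effect size f = 0.39 cannot be reproduced from 11 kg and SD 15, and the power calculation uses a test of average weight although the endpoint is change

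*Protocol article*

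**What the plan says.** The Sample size section of the protocol article names the G*Power F "test between the factors with four groups" and "two evaluation sessions (before and after intervention". Its inputs are "According to the mean difference in the change in body weight (11 kg) and standard deviation of 15" (assumed equal across groups), from which "the calculated effect size *f* is 0.39". It adds an alpha "error probability of 0.05", power 0.80 and a correlation of 0.6 between the two measurements. The result: "The resulting total sample size is 60, meaning 15 in each intervention group". Enrolment is then set at 20 per group to allow for up to 30% dropout.

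Under Study outcomes, "our primary endpoints will be the mean difference in the changes from baseline to 10-week follow-up", compared between the intervention groups. The Statistical analysis section compares the four groups by ANOVA or ANCOVA, describes six pairwise comparisons as primary with Bonferroni correction, uses ANCOVA to adjust for confounding and baseline variables, and sets p < 0.05 ("two-sided) will be considered as statistically significant").

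**The concern.** Two links in the printed calculation do not hold together.

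First, Cohen's f is fixed by the spread of the group means and the common SD. Four equal groups spanning 11 kg with SD 15 have a ceiling for f, and 0.39 lies above it.

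Second, the between-factors option tests whether groups differ in the mean of their repeated measurements. Averaging two measurements with correlation 0.6 multiplies the noncentrality by 2/(1 + 0.6) = 1.25. A test of change takes the difference of the two measurements, so it does not have that gain.

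This is the article's only power justification. At stake is whether the stated 80% belongs to the stated inputs and to the endpoint the trial will analyse.

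**Working it through.** **Inputs.** From Sample size: 4 groups, m = 2 measurements, correlation ρ = 0.6, difference 11 kg, SD 15, alpha 0.05, N = 60, dropout 30% of 80. Not stated: the four group means, and whether 15 is the SD of change or of weight. Both are treated as assumptions below.

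**1. Reproducing the plan's figure.** Between-factors test: λ = N·f²·m/(1 + (m − 1)ρ), with 3 and N − 4 degrees of freedom.
- f = 0.39, N = 60: λ = 60 × 0.1521 × 1.25 = 11.41; power 0.789. The smallest N for 0.80 is 62 (64 if balanced).
- f = 0.3949 gives 0.80 at exactly 60, so 60 agrees with 0.39 up to rounding of f.
- The within-between interaction option with f = 0.39 would need only 20. The between-factors option is therefore the source of 60.

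**2. f from the printed inputs.** f = (population SD of the four group means)/15, with a largest gap of 11 kg:

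| Pattern of means | f | Power at 60, protocol's method |
|---|---|---|
| Two groups at each extreme | 5.5/15 = 0.367 | 0.73 |
| One against three | 4.76/15 = 0.318 | 0.59 |
| Equally spaced | 4.10/15 = 0.273 | 0.46 |
| Two extremes, two in the middle | 3.89/15 = 0.259 | 0.42 |

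At f = 0.367, λ = 60 × 0.1344 × 1.25 = 10.08, and 80% power needs 69 (72 if balanced). Reaching 0.39 takes a difference of 2 × 0.39 × 15 = 11.7 kg or an SD of 5.5/0.39 = 14.1.

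**3. A test that matches the endpoint.** Four-group comparison of change: λ = N·f², where f is the SD of the mean changes divided by the relevant SD.
- Unadjusted, 15 is the SD of change: f = 5.5/15 = 0.367.
- Unadjusted, 15 is the SD of weight: SD of change = 15√(2 × 0.4) = 13.42, f = 0.410.
- ANCOVA on baseline, 15 is the SD of change: SD of weight = 15/√0.8 = 16.77, residual SD = 16.77 × √(1 − 0.36) = 13.42, f = 0.410.
- ANCOVA on baseline, 15 is the SD of weight: residual SD = 15 × 0.8 = 12, f = 5.5/12 = 0.458.

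Evaluable at 30% dropout: 80 × 0.7 = 56. Power for the most favourable pattern, with the other three patterns at 60 in the last column:

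| Analysis | SD 15 is of | Power at 60 | Power at 56 | Other patterns at 60 |
|---|---|---|---|---|
| ANOVA on change | change | 0.62 | 0.59 | 0.34–0.49 |
| ANOVA on change | weight | 0.73 | 0.70 | 0.42–0.59 |
| ANCOVA | change | 0.73 | 0.70 | 0.42–0.59 |
| ANCOVA | weight | 0.83 | 0.80 | 0.51–0.70 |

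The degree of freedom that ANCOVA spends on the baseline covariate changes these by less than 0.001. With 15 as the SD of change, the unadjusted test needs 86 for 80% power (88 if balanced). If f = 0.39 is accepted unchanged, a test on change (λ = 60 × 0.1521 = 9.13) has power 0.68 at 60 and needs 76.

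**4. Diet main effect on change, for reference.** d = 11/15 = 0.733, two-sided 0.05, SD of change 15: power 0.80 at 30 vs 30 and 0.77 at 28 vs 28.

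**The case against.** The ceiling of 0.367 assumes that 11 kg is the largest gap among the four means and that 11 and 15 are exact. The article says neither. If 11.4 and 14.6 were rounded, f = 5.7/14.6 = 0.390. If 11 kg is the diet contrast and the delivery modes differ by a further 4 kg, f = √(5.5² + 2²)/15 = 0.390. This stands: a reader might infer that 0.39 is impossible, but the document supports only that it does not follow from the two printed figures. Neither explanation is stated, and neither touches the mismatch between test and endpoint.

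A reader might also infer that the trial's four-group analysis falls short of 80% whatever is assumed. That does not stand. The Statistical analysis section provides for baseline adjustment, and ANCOVA reaches 0.83 at 60 and 0.80 at 56 if 15 is the SD of weight and the means follow the most favourable pattern. Every other row and pattern in the working is below 0.80.

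Finally, a difference that appears only after treatment is halved in the before/after average: 2.75/15 = 0.183, which gives the between-factors test a power of 0.22 at 60 if 15 is the SD of weight. It is tempting to quote this as the trial's power. It is not, because no section plans to analyse that average. It shows only that the software option does not fit the endpoint.

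**Conclusion.** The point holds as a fault in the printed justification. The step from f = 0.39 to 60 is sound. The step from 11 kg and SD 15 to f = 0.39 cannot be reproduced, and the chosen test does not address change. On the printed inputs the protocol's own method gives at most 0.73 at 60, not 0.80.

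Power for the planned comparison of change at 60 lies between 0.62 and 0.83 for the most favourable pattern of means. It depends on what SD 15 measures and on whether baseline is adjusted for; the ANCOVA figures and the weight-SD figures also use the assumed correlation of 0.6. Less favourable patterns lower every figure. Whether the trial reaches 80% therefore cannot be decided from the article as it stands.

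The Trial status section expects recruitment to finish in January 2021, so this corrects a stated justification and leaves allocation, endpoints and tests unchanged.

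**What to change.** In the Sample size section:

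1. Give the four assumed mean changes and re-derive f from them. If rounding or a delivery-mode effect lies behind 0.39, show it.
2. State whether SD 15 is the SD of change or of weight.
3. Replace the between-factors calculation with one for the planned four-group comparison of change, and say whether it is unadjusted ANOVA or baseline-adjusted ANCOVA.
4. Restate the power at 60 evaluable and at the 56 left from 80 after 30% dropout, for example unadjusted 0.62 and 0.59 with SD of change 15, or ANCOVA 0.83 and 0.80 with SD of weight 15. Say that these are for the most favourable pattern of means.

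The power of the diet main effect on change (0.80 at 30 vs 30, 0.77 at 28 vs 28, SD of change 15) may be reported in addition. It can replace the four-group figure only if that contrast is made the primary comparison, which the Statistical analysis section does not do now.

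Cost: a rewritten paragraph and, under most assumptions, a less favourable power figure. No added participants.

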### Intervention

The participants will be randomly allocated to one of the four aforementioned groups. Accordingly, each participant will be trained in a pre-designed low- or medium-carbohydrate dietetic regimen during a 1-h face-to-face conversation. Everyone will receive a diet plan based on their weight and their daily calorie needs. In the present study, the modified-Paleo diet is defined as 20% carbohydrate, 35% protein, and 45% fat, and the moderate-carbohydrate diet is defined as 40% carbohydrate, 30% protein, and 30% fat. The cooking tips for some of the foods in modified-Paleo menus will be trained via short video clips, and possible questions will be answered. For those receiving a fixed-diet plan, the specified “measuring cups” for each food group and the supplementary information in the booklets will be completely explained.

### Compliance

To determine the adherence to the intervention, individuals will be asked to record their consumption of the main and between-meals food in a checklist given by the investigators every 4 weeks besides the baseline food records. On the whole, six dietary records will be completed by participants during the study (two work days and one holiday, at baseline and after 10 weeks). All records will be immediately revised in order to find possible weaknesses and resolve them. The Nutritionist IV software (First Databank, San Bruno, CA, USA) which is modified for Iranian foods will be used for the evaluation of the dietary records, and the nutrient intake of each participant will be analyzed accordingly. To increase compliance and avoid forgetting the principles of the diets, participants will receive messages on their cell phones and phone calls from the investigators. In addition, serum vitamin C, which is an indicator for high consumption of fruits and vegetables will be examined.

### Intervention safety

No serious side effects have been reported following carbohydrate-restricted diets. To examine the possible side effects that might arise from taking high-protein diets, serum concentrations of creatinine will be quantified at the study baseline and at the end of the trial.

### Outcome measurements

The time points for the assessments of the outcome measures are demonstrated in Fig. 2. All outcome measures will be assessed at the study baseline and at the end of 10 weeks (WK10). Dietary intakes will be assessed at the study baseline, in the middle of the study (WK5), and at the end of 10 weeks (WK10).

**Fig. 2 Fig2:**
[figure not shown]
The time point of enrollment, interventions, and assessments. The “X” refers to what has been done in a specific period of time. EMPs, endothelial ,microparticles; WK, week

### Physical activity assessment

To assess the level of physical activity of each participant, the International Physical Activity Questionnaire is applied, based on the published guidelines [25]. The levels of physical activity will be classified into low, moderate, and high based on the IPAQ criteria and will be expressed as metabolic equivalents (METs) in minutes per week (MET-min/week).

### Anthropometric assessment

Evaluation of anthropometric parameters, including body weight, height, WC, and BMI will be done at the study baseline and end of the trial. Body weight will be measured after a 12-h overnight fasting, without shoes with minimal clothing to the nearest 100 g accuracy, using a weighing calibrated scale (Seca, Hamburg, Germany). Height will be measured by mounted tape, without shoes and at a standing position near to the wall to the nearest 0.1 cm accuracy using a stadiometer (Seca, Hamburg, Germany).

### Body composition assessment

Evaluation of the body composition will be performed via multi-frequency bioelectric impedance analysis (InBody770, Korea) in order to estimate the changes in body fat mass (FM), percentage of fat mass (PFM), skeletal muscle mass (SMM), and visceral fat (VF) during the study. For more accuracy, the patients will be told to stay hydrated and avoid tea, coffee, and alcohol consumption and physical activity 8 h before the test.

### Blood sampling, biochemical, and flow cytometric measurements of EMPs

In a 12-h fasting state, a 10-ml venous blood sample will be taken from each participant at the beginning and the end of the study. After centrifuging for 15 min (3000 rpm), the serum samples will be separated and simultaneously stored at − 80 °C until analysis. Serum lipid profiles (TC, HDL, LDL, and TG) and blood glucose levels will be measured by the enzymatic colorimetric method using commercial kits. Serum insulin, asprosin, chemerin, FGF-21, CTRP-1, PYY, and ghrelin will be measured using an enzyme-linked immunosorbent assay (ELISA) kit. Insulin resistance and insulin sensitivity will be measured by the HOMA-IR and QUICKI formulae, respectively.
$$ \mathrm{QUICKI}=1/\left(\log\ \left(\mathrm{fasting}\ \mathrm{insulin}\ \upmu \mathrm{U}/\mathrm{ml}\right)+\log\ \left(\mathrm{fasting}\ \mathrm{glucose}\ \mathrm{mg}/\mathrm{dl}\right)\right) $$$$ \mathrm{HOMA}-\mathrm{IR}=\left(\mathrm{FBI}\ \left(\mathrm{mU}/\mathrm{l}\right)\times \mathrm{FBS}\ \left(\mathrm{mmol}/\mathrm{l}\right)\right)/22.5 $$

Flow cytometric assessment of endothelial-derived microparticles will be performed according to the study of Mikirova et al. [26]. In order to quantify the level of circulating EMPs, 5–10 ml blood will be collected in tubes containing EDTA. The plasma will be processed within 30 min to 1 h after blood collection by two-step centrifugation. Microparticles in the platelet-poor plasma samples will be quantified by flow cytometry as described in previous studies. Briefly, 50 μl of platelet-poor plasma will be incubated with 5 μl of antibodies: anti CD31, CD42b, and CD144, all from Biolegend (San Diego, CA, USA). After staining, the plasma will be diluted by 350 μl of PBS with 10 mmol citrate; 50 μl of 5 μm AccuCount standard beads (Spherotech, Libertyville, IL) will be added to the sample before analysis to allow calculating of MP values. Samples will be analyzed on a flow cytometer (Quanta, Beckman Coulter) with the relevant FlowJo software, and the final data will be expressed as an absolute count of microparticle/μl.

### Confidentiality

All participant’s information will be stored anonymously following TUMS rules. To respect study participant’s privacy and ensure confidentiality, participants will be identified only by ID numbers in all records and when conducting lab tests by lab staff. All identifying characteristics of participants will be stored in a secure database separate from study data collected during the course of the research. All collected data during different study phases will be kept strictly confidential on password-protected computers in the research team’s office which is accessible only by the study staff. Double data entry and regular recruitment procedures will be employed to enhance data quality during data collection. After the trial is complete, anonymized data will be available to other researchers for conducting a meta-analysis from the corresponding author on reasonable request.

### Statistical analysis

Statistical analyses of all data will be performed using STATA version 12.0 (Stata Corp LP, College Station, TX). The intention-to-treat approach will be used for data analysis in order to handle non-adherence. Data will be expressed as mean (SD). The one-sample Kolmogorov–Smirnov test will be used to verify the normality. If a variable distribution is not normal, the log transformation will be applied. An analysis of variance (ANOVA)/analysis of covariance (ANCOVA) model will be used to compare the values among the four intervention groups. Analysis of variance (ANOVA) and post hoc Bonferroni correction will be used for multiple comparison adjustment. Since we have 4 intervention groups (1, modified-Paleo diet with calorie counting; 2, modified-Paleo diet with a fixed diet plan; 3, medium-carbohydrate diet with calorie counting; and 4 medium-carbohydrate diet with a fixed diet plan), we will have six possible pairwise comparisons across the groups (1 with 2, 1 with 3, 1 with 4, 2 with 3, 2 with 4, 3 with 4). By these primary comparisons, we will be able to compare the effects of diets (low vs moderate carbohydrate) and delivery modes (calorie counting vs fixed diet plan) on primary outcomes. Further, there are two modules, by which confidence intervals can also be adjusted along with *p*-value for multiple comparisons. “Pwmean” and “pwcompare” modules allow for performing all pairwise comparisons using Tukey, Bonferroni, or Dunnett. An analysis of covariance (ANCOVA) will be applied to adjust the effects of confounding and baseline variables. *p* < 0.05 (two-sided) will be considered as statistically significant. Besides the null hypothesis significance testing (NHST), appropriate effect size and its 95% confidence interval will also be analyzed to provide more reasonable justification about results. Cohen’s *d* effect size, measured as the mean difference in change divided by the pooled standard deviation of the change, will be reported along with its 95% CI. Cohen’s *d* is defined as standardized mean difference (SMD) and is classified as small (*d* = 0.2), medium (*d* = 0.5), or large (*d* = 0.8) [27]. Multiple imputation will be used to correct missing data. The SAMPL guideline will be used for statistical analysis in this study [28].

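### An uncorrected Kolmogorov–Smirnov test on the trial data picks the analysis scale, with a log transform of an unnamed variable as the only remedy; the cost is power and clarity for CTRP6 and the other biomarkers

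*Protocol article*

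**What the plan says.** All but one of the relevant statements stand in the Statistical analysis section of the protocol article.

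- The test: "The one-sample Kolmogorov–Smirnov test will be used to verify the normality". Its reference mean and SD are not stated, and no correction for estimating them is named.
- The remedy: "If a variable distribution is not normal, the log transformation will be applied". The text does not say whether the variable is a raw measurement, a change or a model residual. It offers nothing if the log cannot be taken or does not help.
- The model: an ANOVA/ANCOVA "model will be used to compare the values among the four intervention groups", with ANCOVA that "will be applied to adjust the effects of confounding and baseline variables".
- The effect measure: Cohen's d, "measured as the mean difference in change divided by the pooled standard deviation of the change". Summaries are means with SDs, with no exception for logged variables.

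The Study outcomes section sets the scale of the primary comparison: "our primary endpoints will be the mean difference in the changes from baseline to 10-week follow-up". These endpoints are weight, body fat mass and CTRP6.

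**The concern.** Three features of the rule do not fit this trial.

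1. **The test is miscalibrated.** The one-sample KS critical values hold for a fully specified reference distribution. If mean and SD come from the same sample, the fitted curve lies closer to the data than those values allow for, and the test becomes very conservative. Passing it says little about normality.
2. **The remedy does not match the endpoint.** The primary endpoints are changes, and in a weight-loss trial most changes are negative. A log is not defined there.
3. **The scale is chosen from the trial data.** Whether a marker is analysed as a difference or on the log scale depends on one sample test, and could differ between markers or between visits of the same marker. ANOVA and ANCOVA also rest on the residuals, not on the distribution of the raw variable.

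At stake are the precision and readability of the biomarker results. They include CTRP6, one of the primary endpoints, any of which can by itself establish trial success.

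**Working it through.** **Inputs from the article.** 60 analysable patients (15 per group), 80 enrolled (20 per group), correlation between visits 0.6, two-sided alpha 0.05. The article gives no figure for the normality rule itself. The N = 60 used below can be reproduced: λ = f²·N·m/[1 + (m−1)ρ] = 0.39² × 60 × 2/1.6 = 11.4 with 3 and 56 df gives power 0.789. With f = 0.3949, which also rounds to 0.39, power is 0.800.

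**Assumptions.** Markers are lognormal with log-SD 0.3 to 1.0. The article gives no biomarker distribution, so this is a range, not an estimate.

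**Step 1: how often the test rejects.** KS applied to (x − mean)/SD against N(0,1), nominal 5%, 4,000 samples per cell:

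| n | normal data | log-SD 0.3 | 0.5 | 0.7 | 1.0 |
|---|---|---|---|---|---|
| 15 (one arm) | 0% | 0.1% | 1% | 3% | 10% |
| 20 (one arm) | 0% | 0.2% | 1% | 6% | 20% |
| 60 (pooled) | 0% | 2% | 18% | 50% | 90% |
| 80 (pooled) | 0% | 3% | 29% | 71% | 98% |

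Repeat runs moved these by a point or three (16% at n = 60 and log-SD 0.5; 72% at n = 80 and log-SD 0.7). At n = 60 and log-SD 0.3/0.5/0.7/1.0, the Lilliefors version detects 36%/76%/95%/100% and Shapiro–Wilk 66%/97%/100%/100%.

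**Step 2: if the variable is the change (week 10 minus baseline).** The share at or below zero is Φ(−mean/SD). For assumed weight changes:

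- mean −3 kg, SD 3: Φ(1) = 84%
- mean −5 kg, SD 5: Φ(1) = 84%
- mean −5 kg, SD 3: Φ(1.67) = 95%
- mean −8 kg, SD 4: Φ(2) = 98%

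For a lognormal marker whose median falls by about 10% (log shift −0.1, correlation 0.6 on the log scale), the share is 64%, 59%, 56% and 54% at log-SD 0.3, 0.5, 0.7 and 1.0. None of these values has a log.

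**Step 3: if the variable is the raw value.** With n = 60, correlation 0.6 on the log scale and no treatment effect, the KS verdicts at baseline and week 10 disagree in about 26% of trials at log-SD 0.5 and 45% at 0.7. The text does not say which verdict governs.

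**Step 4: consequence for the four-group comparison, N = 60.** Here KS is run on raw baseline values, and the log scale is used at both visits if it rejects. The assumed diet effect is 0.9 SD of the log change.

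| log-SD | ANOVA on change: KS rule | ANOVA: log fixed | ANCOVA: KS rule | ANCOVA: log fixed |
|---|---|---|---|---|
| 0.3 | 0.74 | 0.82 | 0.87 | 0.90 |
| 0.5 | 0.64 | 0.81 | 0.84 | 0.90 |
| 0.7 | 0.67 | 0.82 | 0.82 | 0.89 |
| 1.0 | 0.78 | 0.82 | 0.87 | 0.89 |

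Before rounding, the loss is 4 to 18 points for ANOVA on change and about 2 to 7 points for ANCOVA (10,000 runs). Other ANCOVA runs gave about 1 to 5 points, so about 1 to 7 is a fair range. Type I error under the rule was 0.036–0.050 for ANOVA and at most 0.055 for ANCOVA, so there is no inflation beyond simulation error.

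**The case against.** There are several good answers in favour of the plan.

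- **The rule can be applied.** A reader might infer that it is impossible to carry out. That holds only if the log is taken of the change. Weight, fat mass, concentrations and microparticle counts are in practice positive, and the model is said to compare values with adjustment for baseline. Logging both visits is therefore open under the text. What stands is that the text does not say so, while the endpoint and Cohen's d are both defined on the change.
- **Strong skew is usually caught.** A reader might infer that skewed markers will simply pass the test. In the pooled sample that is false at log-SD 1.0 (90–98% detected), and the article does not say that the test is run by arm. What stands is the miss rate at log-SD 0.3–0.5, and about 30–50% missed at 0.7.
- **Weight and fat mass hardly reach the log branch.** A test that almost never rejects near-normal data leaves them untransformed, which is also what is recommended here. This is correct and narrows the point to CTRP6 and the other markers.
- **Estimated parameters are an inference.** True, but no reference values are given and no correction is named.
- **An article may leave detail to the full protocol or analysis plan.** That covers residual checks and the summary of logged variables. It does not cover a named test and a named remedy that the article itself fixes.

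**Conclusion.** The point holds as a modest, cheap improvement. The article fixes a test that is badly calibrated on its natural reading, lets it choose the scale, and gives one remedy without naming the variable to which it applies.

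The harm is lost power and an effect scale that depends on the sample: 4 to 18 points for ANOVA on change and about 1 to 7 for baseline-adjusted ANCOVA. It falls on CTRP6 and the secondary and exploratory markers. These sizes rest on lognormal markers with log-SD 0.3–1.0, a diet effect of 0.9 SD of the log change, and KS with estimated mean and SD. If the markers are close to normal, little is lost.

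A reader might go further and conclude that the analysis scale is wrong or the p-values invalid. The documents do not support that. Type I error stays at its nominal level in the simulations, and nothing in the article shows how skewed these markers are.

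**What to change.** Remove the normality pre-test and state the scale for each outcome before the data are seen.

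- **Weight and body fat mass:** ANCOVA of the untransformed week-10 value (or change) on baseline, with residual checks.
- **Positive markers expected to be skewed** (the CTRP marker, insulin, leptin, microparticle counts, other ELISA markers): ANCOVA of the log week-10 value with log baseline as covariate. Check residuals, and report geometric mean ratios with 95% CIs in place of differences in means.

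The cost is wording only; sample size and data collection do not change. The downside is that marker effects are read as ratios, not as differences in concentration, and Cohen's d for those markers would have to be defined on the log scale or dropped.

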## Methods/design

This randomized single-blind clinical trial with a factorial design will be conducted in Tehran, Iran. All participants will be asked to complete and sign the written informed consent form before enrollment. The study has already been approved by the bioethics committee of Tehran University of Medical Sciences (No. IR.TUMS.VCR.REC.1396.2046).

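### The 2×2 factorial trial takes six Bonferroni pairs among four arms as its primary comparisons; these are not the test that was powered, and no main effect or interaction is stated

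*Protocol article*

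**What the plan says.** Methods/design states the design: "This randomized single-blind clinical trial with a factorial design will be conducted in Tehran, Iran". The Background also calls the trial factorial, and the factors are diet (modified-Paleo or moderate-carbohydrate) and delivery mode (calorie counting or fixed plan).

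The Sample size section uses an F "test between the factors with four groups" and "two evaluation sessions (before and after intervention"). Its inputs are: "According to the mean difference in the change in body weight (11 kg) and standard deviation of 15", f = 0.39, alpha 0.05, power 0.80 and correlation 0.6. The result is 60 participants, 15 per arm, raised to 20 per arm for dropout.

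The Statistical analysis section compares the four arms by ANOVA/ANCOVA. It then says: "Analysis of variance (ANOVA) and post hoc Bonferroni correction will be used for multiple comparison adjustment". It lists the six pairs and assigns them their role: "By these primary comparisons, we will be able to compare the effects of diets (low vs moderate carbohydrate) and delivery modes". It also says: "An analysis of covariance (ANCOVA) will be applied to adjust the effects of confounding and baseline variables". It contains no contrast that averages over the other factor, and no diet-by-mode interaction.

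**The concern.** A 2×2 factorial trial asks two questions, and each can be answered with every randomised participant: compare the two diets across both delivery modes, and the two delivery modes across both diets. The plan instead splits each question over single-arm pairs. In the protocol's numbering, 1 vs 3 and 2 vs 4 isolate diet, while 1 vs 2 and 3 vs 4 isolate delivery mode. Pairs 1 vs 4 and 2 vs 3 change both factors at once, yet they take two of the six Bonferroni shares.

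Each pair uses half of the participants at one sixth of the alpha. The comparisons called primary therefore have much less power than a marginal contrast would have, and they are not the comparison for which the protocol states 80%. A diet effect that is equal in both delivery modes can easily be significant in one and not in the other. That pattern invites a claim of interaction that no planned test supports.

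**Working it through.** **Inputs** (Sample size and Statistical analysis sections): difference 11 kg, SD 15, 15 evaluable or 20 enrolled per arm, alpha 0.05 two-sided, six pairs, so 0.05/6 = 0.00833 each. Assumptions: 15 is the SD of the change; the diet effect is 11 kg in both delivery modes; there is no delivery effect and no interaction.

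**1. The protocol's own figure.** For the between-factors F test with m = 2 sessions, λ = f²·N·m/(1 + (m−1)ρ). At N = 60: λ = 0.39² × 60 × 2/1.6 = 11.41, with 3 and 56 df. Power is 78.9%. The smallest N for 80% is 62, or 60 with an unrounded f near 0.395. The stated 60 is reproduced within rounding, so the 80% is the power of the four-group F test.

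**2. One diet pair (1 vs 3 or 2 vs 4) at 0.00833.** Noncentrality is 11/(15·√(2/n)), with pooled error df 4n − 4.
- n = 15: 2.01 against a critical t of 2.74; power 24.4%.
- n = 20: 2.32 against 2.71; power 35.5%.
- n = 14 (30% loss from 20): power 22.3%.
- 80% power for one such pair needs about 46 per arm.

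**3. Both diet pairs considered together.** The two pairs share no participants, so roughly 1 − (1 − p)² gives at least one and p² gives both. Simulation with the shared error variance gives:
- at least one significant: 42% (n = 15), 58% (n = 20);
- both significant: 7% and 13%.

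**4. The four-group F test on the change under this pattern.** The SD of the means (0, 0, 11, 11) is 5.5, so f = 5.5/15 = 0.367. One-way power is 62% at N = 60 and 77% at N = 80.

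**5. Diet main effect, two arms against two.** Noncentrality is 11/(15·√(2/2n)).

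| Participants | alpha 0.05 | alpha 0.025 |
|---|---|---|
| 28 vs 28 | 77% | 67% |
| 30 vs 30 | 80% | 70% |
| 40 vs 40 | 90% | 84% |

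**6. Precision with 80 participants (76 df).**
- Pair, unadjusted 95%: 1.992 × 15 × √(2/20) = 9.4 kg.
- Pair, Bonferroni: 2.709 × 15 × √(2/20) = 12.9 kg.
- Main effect, unadjusted 95%: 1.992 × 15 × √(2/40) = 6.7 kg.

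**7. Sensitivity to the SD.** If 15 is the SD of change, baseline adjustment multiplies the variance by (1 − 0.6²)/(2(1 − 0.6)) = 0.80, so the SD is 13.4. If 15 is the SD at one visit, the change has SD 15·√0.8 = 13.4 and the baseline-adjusted SD is 15·√0.64 = 12.
- SD 13.4: one pair 32% (n = 15) to 46% (n = 20); at least one 53% to 70%.
- SD 12: one pair 42% to 58%; at least one 65% to 81%.

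The main effect gains from the smaller SD as well: at SD 13.4 and alpha 0.05 it has 88% (30 vs 30) and 95% (40 vs 40).

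**The case against.** The strongest reply has four parts.

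First, a reader might conclude that the diet question has 24% to 35% power where the protocol promises 80%. The documents do not support that. The 80% is stated for a different test, and the lower figure is for one pair when the plan offers two diet pairs. Nor can it be said that a real 11 kg effect would usually be missed. With 20 per arm at least one diet pair is significant in 58% of trials, the planned four-group test has 77%, and on the most favourable SD reading at least one pair reaches 81%. This part of the reply stands.

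Second, setting a pair at 0.05/6 beside a main effect at 0.05 flatters the main effect, since there are two factors. This also stands, and it is why the 0.025 figures are shown. The gap narrows but remains: 70% to 84% against 42% to 58% for at least one pair at the same SD.

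Third, effects within a delivery mode are a legitimate target if diet and mode interact. That is so, and the main-effect power assumes no interaction. But the plan neither tests nor estimates an interaction, and pairs 1 vs 4 and 2 vs 3 compare whole packages, which answers neither stated question.

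Fourth, a reader might infer that the analyst may pick the multiplicity method after seeing the data, because the article says that two Stata "modules allow for performing all pairwise comparisons using Tukey, Bonferroni, or Dunnett". That sentence describes what software can do; Bonferroni is the method the article says will be used. The ANOVA/ANCOVA choice and the covariate list are details that an article commonly leaves to the full plan. Neither is part of this point.

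**Conclusion.** The point holds as a mismatch of design, sizing and analysis. The trial is called factorial, it is sized on a four-group F test, and its diet and delivery questions are assigned to six adjusted pairs, two of which isolate neither factor.

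On the protocol's inputs a single diet pair has about 24% to 35% power, and no SD reading tried lifts one pair above 58%. The marginal diet contrast has about 80% to 90% at 0.05 in the same participants, and its unadjusted interval is narrower by a factor of √2.

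These sizes rest on 11 kg, on SD 15 being the SD of change, and on an equal diet effect in both delivery modes. If the effect differs by mode, the main effect becomes an average and its power changes. The mismatch itself needs none of these assumptions, because it is visible in the text.

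**What to change.** For each primary outcome, make the primary model a two-way ANCOVA of the week-10 value on diet, delivery mode and their interaction, with the baseline value as covariate.

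- Name the diet main effect as the primary contrast and the delivery-mode main effect as the second. State the alpha rule between them: a fixed sequence, or 0.025 each.
- Report the interaction with its 95% CI.
- Keep 1 vs 3, 2 vs 4, 1 vs 2 and 3 vs 4 as supportive, and remove 1 vs 4 and 2 vs 3 from the primary family.
- Restate the power for the contrasts that are called primary.

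The cost is analysis wording and one power recalculation; no extra participants, visits or assays are needed. The downside is that a main effect averages over the other factor, so the interaction estimate must stand beside it. With this sample size that estimate will be imprecise, and a non-significant interaction should not be read as proof that there is none.
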